#### Strategies to improve adherence to interventions

2.7.3

This study will ensure participant compliance with the following three strategies. (1) While recruiting participants and seeking their signed consent forms, researchers will clarify in great detail the participant requirements for the duration of observation and establish a good relationship with them to gain their trust. (2) Throughout the trial, participants will be educated in a thorough way about disease management and preventive practices. This involves educating them on the nature of their illness, why it’s important to stick with treatment, and steps to avoid any potential complications. By educating participants about their own care, we hope to engage better with medical advice and actively participate. (3) The intervention group’s interaction with the system on the portal will be monitored by the study team weekly to review their engagement.

### Outcomes

2.8

#### Primary outcomes

2.8.1

The primary outcome is the change in CAT scores (COPD Assessment Test), measured at baseline, discharge, and post-intervention.

#### Secondary outcomes

2.8.2

Changes in self-management behaviors: including diet, physical activity, medication adherence, smoking management, alcohol management, sleep management, quality of life, and activities of daily living.

Social Cognition and Psychological Factors: COPD knowledge literacy, self-efficacy, depression, anxiety, stress, and social support.

Control of physiological indicators: cough, breathlessness, blood pressure, height, and weight.

30-days readmission rate: additionally, recruitment rates, dropout rates, and reasons for withdrawal will be collected. To assess the homogeneity of the data, demographic characteristics and outcomes of those who dropped out, as well as those with resistance to the trial, will be compared during the data analysis process.

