### Randomization and blinding

2.2

In this research, a computer-generated random number sequence will be applied in randomization. Patients will be assigned to intervention and standard care groups in a 1:1 ratio. Randomization will be carried out prior to their hospital admission. Through this process, every patient will be assigned to their corresponding study group based on a predetermined sequence to ensure randomness and equity of allocation. Upon entering their ward, each patient will receive a unique code that is equivalent to the random number sequence for facilitation of smooth and uninterrupted recruitment. Once randomization is completed, patients will be transferred to their respective ward depending on their assigned groups. Specifically, intervention patients will be admitted to Ward A, with patients in the control arm going to Ward B to avoid possible cross-contamination between different treatments.

In order to maintain confidentiality of sequence allocation, an independent team member not involved in participant registration or in intervening in any way in the allocation process will perform randomization. This step aims to avoid revealing the randomization sequence during the study. The allocation outcome will then be communicated by the independent team member to the intervention team so that neither the participant registration team nor intervention team knows beforehand against which group a participant is registered.

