### Sample size

2.4

This RCT will be conducted in two sequential phases. The first phase serves as a pilot study aiming to obtain preliminary estimates of the intervention’s effect size, variability, and feasibility parameters. These pilot data will provide empirical inputs for calculating the appropriate sample size required for the subsequent full-scale RCT.

In this pilot phase, the primary objective is not hypothesis testing but to estimate outcome variance and effect size with sufficient precision to inform future sample size determination. Following commonly recommended practices for pilot RCTs (17), approximately 25 participants per group (about 50 in total) will be recruited. Considering an anticipated 10%–20% attrition rate, the total recruitment target is set at 60 participants (30 per group).

The effect size derived from this pilot phase will then be used to conduct a formal power analysis to determine the optimal sample size for the main RCT, ensuring adequate statistical power to test the study hypotheses.

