### Statistical analysis

2.11

We will collect quantitative data using a structured questionnaire and then input it into Microsoft Excel for analysis. All major analyses will follow intention to treat (ITT) and will undergo protocol compliant (PP) analysis for sensitivity testing. Descriptive statistics will be used to summarize feasibility variables such as starting information, number of participants, and system usage. For continuous data, the mean and standard deviation of normally distributed data, as well as the median and 25th to 75th percentile of non-parametric data, will be provided. To compare the untreated group and the group measured once, independent sample *t*-tests and their non-parametric analogues will be used. The categorical data will be expressed in frequency and percentage, and analyzed using chi square test. The normality of the data will be tested using the Kolmogorov Smirnov test. Under the assumption of random missing data, established multiple imputation methods will be used in appropriate circumstances to handle the missing data. We will examine and compare the missing and wear patterns between each group to identify potential differences in dropout rates, and conduct sensitivity analysis to compare estimated and complete case outcomes. For the main experiments, the focus will be on using a linear mixed effects model to evaluate the main outcome indicators. For secondary outcomes such as self-management and psychosocial/cognitive outcomes, analysis will use similar mixed effects models or simpler comparison methods, depending on the nature and timing of data collection. In addition, exploratory age stratification analysis can be conducted to examine the potential heterogeneity of intervention effects across different age groups in a descriptive manner. Given the pilot nature of the study, the results should be interpreted with caution. The measurement criteria used by the system, such as the number of questions, will be summarized in a descriptive manner and can be included as covariates in exploratory analysis to better understand compliance patterns; these analyses will be seen as hypothesis generation rather than validation. All statistical tests are two-sided, with a significance level of 0.05. Data analysis will be conducted using IBM SPSS Statistics (version 24.0; SPSS Inc., Chicago, Illinois, USA and Stata (version 14.0); StataCorp, College Station, TX, The United States) conducted.

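### Agreement between imputed and complete-case results cannot show that missing at random is safe, and 6 to 12 dropouts are too few to establish homogeneity

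*Protocol article*

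**What the plan says.** Section 2.8.2 (Secondary outcomes) says that recruitment rates, dropout rates and reasons for withdrawal will be collected. It then sets up a comparison of patients who left: "To assess the homogeneity of the data, demographic characteristics and outcomes of those who dropped out". It names no test, threshold or consequence.

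Section 2.11 (Statistical analysis) assumes that missing data are random and uses multiple imputation where appropriate. It compares missingness between arms to look for differences in dropout, and it will "conduct sensitivity analysis to compare estimated and complete case outcomes". A per-protocol analysis is also planned as sensitivity testing. The general rule is "All statistical tests are two-sided, with a significance level of 0.05". No analysis that departs from missing at random is stated.

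Section 2.4 (Sample size) gives the scale. It says "approximately 25 participants per group (about 50 in total) will be recruited", and "Considering an anticipated 10%–20% attrition rate" the target becomes 60, or 30 per group. The same section carries the pilot's effect size into the power calculation for the main trial.

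**The concern.** The CAT is patient-reported, and section 2.2 accepts that participants cannot be blinded. Section 5 (Discussion) itself cites high dropout as a constraint on existing mobile health interventions. Dropout related to how patients fare, and unequal between arms, is therefore plausible.

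The planned comparison of imputed with complete-case results answers a narrower question: whether dropout related to observed data matters. It does not address outcomes that differ from what the observed data predict. The comparison of dropouts in 2.8.2 cannot fill that gap, for two reasons. Outcomes after a patient leaves are not observed, and what is observed comes from very few people.

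If agreement on either check were taken as support for missing at random, a biased CAT difference could be treated as robust and used to size the main trial.

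**Working it through.** **Inputs.** From 2.4: about 50 evaluable, 10%–20% attrition, 60 recruited. From 2.2: 1:1 allocation. From 2.11: two-sided 0.05. Every other value below is an assumption and is marked as such.

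**The plan's own figure.** Inflating 50 by 1/(1 − d) gives:
- 50/0.90 = 55.6, so 56
- 50/0.85 = 58.8, so 59
- 50/0.80 = 62.5, so 63

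The target of 60 corresponds to attrition of 16.7% (50/0.833 = 60), within the stated range. Dropouts number 60 × 0.10 = 6 to 60 × 0.20 = 12.

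**Precision of dropouts versus completers.** In SD units, SE = √(1/a + 1/b), with 58 degrees of freedom and t = 2.002. The miss rate is 1 minus the power of a two-sided 5% t-test (noncentral t, noncentrality = difference/SE). The differences of 0.5, 0.8 and 1.0 SD are assumptions.

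| Dropouts vs completers | SE | 95% CI half-width | Missed at 0.5 SD | Missed at 0.8 SD | Missed at 1.0 SD |
|---|---|---|---|---|---|
| 6 vs 54 | 0.430 | 0.86 SD | 79% | 55% | 37% |
| 9 vs 51 | 0.362 | 0.72 SD | 72.5% | 41% | 22% |
| 12 vs 48 | 0.323 | 0.65 SD | 67% | 32% | 14% |

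The half-width needs no assumed effect. The difference detectable with 80% power is (1.96 + 0.84) × SE, which is 1.21 SD with 6 dropouts and 0.90 SD with 12.

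**Between-arm dropout.** Exact binomial enumeration at 30 per arm, with assumed rates:
- 10% vs 20%: missed 81% of the time by chi-square, 90% by Fisher's test.
- 10% vs 30%: missed 50% by chi-square, 63% by Fisher's test. Here SE = √(0.1 × 0.9/30 + 0.3 × 0.7/30) = 0.10, so the 95% half-width is about 20 percentage points.

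**Imputed versus complete-case.** Large-sample simulation with no true effect. Dropout depends on the end-of-intervention outcome (log-odds slope 1 per SD, worse outcomes more likely to leave) and is 10% in one arm and 30% in the other (20% overall, the top of the plan's range). Assumed correlations are baseline–end 0.5, discharge–end 0.7 and baseline–discharge 0.6. If the heavier dropout is in the AI-HEALS arm, a negative value favours AI-HEALS.

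| Analysis | Bias, 10% vs 30% |
|---|---|
| Complete-case, unadjusted | -0.16 SD |
| Complete-case, baseline-adjusted | -0.12 SD |
| Imputation from baseline | -0.13 SD |
| Imputation from baseline and discharge | -0.09 SD |

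All four err in the same direction. The baseline-adjusted complete-case and baseline-imputed results nearly coincide while both are wrong. At 10% vs 20% with a baseline–end correlation of 0.6, the biases are about -0.08 (unadjusted complete-case), -0.05 (adjusted complete-case) and -0.05 (imputation from baseline). With dropout equal across arms under the same mechanism, the net bias is about zero.

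When dropout depends on baseline only (one arm, 20% dropout, correlation 0.6), the bias in that arm's mean is about -0.11 SD for complete-case and about 0 for imputation. In that situation the planned comparison does reveal something.

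**The case against.** The strongest reply is that the protocol contains no rule to attack. Section 2.8.2 says only that groups will be compared. Section 2.11 looks for differences in dropout rather than declaring equality, and urges caution because this is a pilot. Section 2.4 says hypothesis testing is not the primary objective. Reasons for withdrawal are collected, and section 2.6 plans interviews with withdrawers where possible. Detailed missing-data sensitivity analysis is commonly left to a statistical analysis plan, which is not shown.

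Much of this stands. A reader might infer that informative dropout would be passed as absent. The documents do not support that, since the 0.05 level applies where a test is run and nowhere makes non-significance a certificate of homogeneity.

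A reader might also infer that the imputed and complete-case analyses share one identical bias, for example -0.20 SD each. That figure follows from assuming a constant 1-SD worsening in dropouts' unseen outcomes and a 3:1 dropout split: (0.30 − 0.10) × 1 SD = 0.20 SD. The two results then match by construction. With outcome-dependent dropout the sizes differ by model, and discharge CAT, which the plan measures, recovers part of the loss.

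The reply does not remove the narrower point. The protocol does name its missing-data check, and that check cannot test the assumption it accompanies. The per-protocol analysis, withdrawal reasons and interviews give context, but none shows how the estimate would move if unseen outcomes were worse than predicted.

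**Conclusion.** The point holds as a limit on what the stated checks can show. Agreement between imputed and complete-case results does not make missing at random safe, and an apparent lack of difference among 6 to 12 dropouts does not establish homogeneity.

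The 0.65–0.86 SD half-width rests only on the plan's figures. The 67–79% miss rate rests on an assumed 0.5-SD difference tested at 0.05 and falls to 32–55% at 0.8 SD and 14–37% at 1.0 SD. The bias of about -0.09 to -0.16 SD rests on outcome-dependent dropout that differs by arm. If the CAT SD were 6 to 8 points (an assumption), that is 0.09 × 6 = 0.5 to 0.16 × 8 = 1.3 points.

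For a 60-patient pilot this is a cheap and worthwhile improvement. It is not a contradiction or a stated error.

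**What to change.** **Section 2.11.** Keep the complete-case comparison as description. Add delta-adjusted multiple imputation of end-of-intervention CAT: worsen the imputed values over a stated range, in the AI-HEALS arm alone and then in both arms. Report how the estimate moves and the delta at which it reaches zero, before the effect size is carried into the main-trial sample size. The effect is easy to read. With dropout proportion p in the AI-HEALS arm and q in the control arm, a shift of delta moves the estimate by p × delta in the first case and (p − q) × delta in the second. At p = 0.20, each CAT point of delta in the AI-HEALS arm alone moves the difference by 0.2 points.

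**Section 2.8.2.** Report dropout-versus-completer differences and the between-arm difference in dropout rate with 95% CIs. State that a wide interval is not evidence of homogeneity.

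**Cost.** A few sentences and a few extra runs of the imputation already planned, with no new data or patients. The robustness statement may become less favourable.

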### Variables measurement

2.9

Sociodemographic variables will be obtained at baseline. Physical examinations and questionnaires will be completed at baseline, discharge, and end of intervention, and at 3, 6, and 9 months post-intervention (Table 1).

**TABLE 1 T1:** The schedule of enrollment, interventions, and assessments.

Study period	Recruitment	Intervention		Follow-up		
Timepoint	0	Discharge	3 months	3 months	6 months	9 months
Eligibility screen	√					
Informed consent	√					
Allocation	√					
Sociodemographic variables	√					
CAT	√	√	√	√	√	√
mMRC	√	√	√	√	√	√
CET	√	√	√	√	√	√
PHQ4	√	√	√	√	√	√
PSSS-SF	√	√	√	√	√	√
NGSES-SF	√	√	√	√	√	√
EQ-5D-5L	√		√	√	√	√
Smoking	√		√	√	√	√
Alcohol consumption	√		√	√	√	√
B-PSQI	√		√	√	√	√
FCS-SF	√					
eHEALS	√					

B-PSQI, The new Brief Version of the Pittsburgh Sleep Quality Index-Short Form; CAT, COPD Assessment Test; CET, Cough Evaluation Test; eHEALS, The eHealth Literacy Scale; EQ-5D-5L, EuroQol-5 Dimensions 5 Levels; FCS-SF, The Family Communication Scale-Short Form; IPAQ-SF, The International Physical Activity Questionnaire Short Form; mMRC, Modified Medical Research Council; PHQ-4, the abbreviated Patient Health Questionnaire-4; PSSS-SF, The Perceived Social Support Scale; NGSES-SF, The New General Self-Efficacy Scale-Short Form; SREBQ, The Self-Regulation of Eating Behavior Questionnaire.

After discharge, we will maintain contact with participants via WeChat, telephone, or text messages to ensure they stay well-informed and remain actively engaged. During these interactions, participants will receive timely updates on study progress, solutions to any emerging issues, and timely reminders for upcoming follow-up assessments.

Standardized data entry for this study will be conducted using an electronic data capture (EDC) system. First, double data entry will be performed by two independent operators to ensure accuracy, followed by logical validation checks on all raw data. Sensitive information will be encrypted using the Unicode encoding scheme. Data will be stored on password-protected servers with role-based access control (where only authorized researchers can access de-identified data), and a real-time backup system will be deployed to off-site cloud storage to ensure data integrity and disaster recovery capabilities.

Once we have obtained relevant information from participants, we will take instant steps to remove all identifiable personal details in an effort to maintain confidentiality of data. Throughout this process, identifiable personal details will be coded with a unique code. This key connecting such codes to real identity details will be accessible by only a few authorized members of our research team and will be kept in a distinctly separate location. We will never provide any personal details to third parties until such time that we receive explicit, informed consent from the participant. All members of the research team will be required to enter into confidentiality agreements that will help guarantee that every team member maintains the highest standards of privacy. Throughout the study from beginning to end, and after it is finished, all personally identifiable information will be stored securely on specified servers that only officially designated researchers can access.

Socio-demographic variables: gender, age, marital status, location, average household size, educational level, occupation, as well as clinical information, including the degree of lung function and detailed medical history.

Anthropometric variables: height, weight, waist circumference, and blood pressure will be measured twice for each participant using certified instruments. Height and weight will be measured using fully calibrated, certified electronic devices. The body mass index (BMI) will be calculated by dividing weight (in kilograms) by height (in meters squared). Waist circumference will be measured at the level of the umbilicus using a flexible tape measure. Blood pressure will be measured using a validated automatic blood pressure monitor to assess both systolic and diastolic pressures.

Respiratory function: it will be assessed using a series of pulmonary function tests (PFTs) that provide insights into lung mechanics and gas exchange, including the percentage of forceful expiratory volume predicted in 1 s (FEV1) and FEV1/forceful lung volume (FVC) (18). FEV1 indicates the volume of air exhaled in the first second after administration of bronchodilators, whereas the FEV1/FVC ratio indicates the degree of airway obstruction.

### Questionnaires

2.10

CAT: the COPD Assessment Test is used to assess the impact of COPD on patients’ health and daily life (19), covering eight aspects: cough, sputum production, chest tightness, activity level, ability to perform daily activities, social activities, sleep, and energy levels. Each question is scored on a 6-point scale (0–5), with the total score ranging from 0 to 40. Based on the total score, COPD severity is categorized as follows: 0–10 (mild impact), 11–20 (moderate impact), 21–30 (severe impact), and 31–40 (very severe impact).

Modified Medical Research Council (mMRC) Dyspnea Scale: the mMRC scale is primarily used to assess the degree of dyspnea in COPD patients (20). It categorizes the severity of shortness of breath based on the level of activity at which it occurs, with 5 levels (0–4). A score of 0–1 indicates minimal symptoms, scores of 2 and above indicate more frequent symptoms, and a score of 4 represents the most severe dyspnea, where the patient experiences difficulty breathing even with minimal exertion.

Cough Evaluation Test (CET): the Cough Evaluation Test consists of five items (21), including “daytime cough severity,” “impact of cough on sleep,” “severity of coughing episodes,” “impact of cough on daily activities,” and “anxiety caused by coughing.” The CET uses a Likert scale for scoring, with each item rated from 1 to 5, yielding a total score range of 5–25. A higher score indicates more severe cough symptoms or greater impact.

The assessment of depression and anxiety will be conducted using the Patient Health Questionnaire-4 (PHQ-4). This is a brief self-report tool designed to evaluate an individual’s depression and anxiety symptoms over the past 2 weeks (22). The PHQ-4 consists of four items, which assess two dimensions: the first two items focus on depressive symptoms, while the latter two address anxiety symptoms. Each item is rated on a four-point scale: “Not at all” (0 points), “Several days” (1 point), “More than half of the days” (2 points), and “Nearly every day” (3 points), with a total score range of 0–12. The PHQ-4 demonstrates high validity and reliability, with a Cronbach’s alpha coefficient of 0.833 in research studies conducted in China.

The Perceived Social Support Simplified Scale (PSSS-SF) is designed to assess an individual’s perception of social support (23). The scale consists of three items, each corresponding to a different dimension of support: family support (Item 1), friend support (Item 2), and other forms of support (Item 3). Each item is rated on a 7-point Likert scale, ranging from 1 (strongly disagree) to 7 (strongly agree), with a total score ranging from 3 to 21. A higher score indicates a greater perception of social support, reflecting the effectiveness of the individual’s social network in providing emotional and practical assistance.

The New General Self-Efficacy Scale (NGSES-SF) is used to assess an individual’s confidence in their ability to successfully complete specific tasks or overcome challenges (24). This scale also consists of three items, which measure three dimensions of self-efficacy: the level or degree of capability (Item 1), the strength of confidence (Item 2), and the generalizability of this confidence (Item 3). Responses are rated on a 5-point Likert scale, with scores ranging from 1 (strongly disagree) to 5 (strongly agree), and the total score ranges from 3 to 15. Higher scores directly reflect a greater level of self-efficacy, indicating stronger confidence and coping ability.

The EQ-5D-5L scale (EuroQol-5 Dimensions 5 Levels) will be used to assess quality of life (25). This scale specifically measures five key health dimensions: mobility, self-care, usual activities, pain/discomfort, and anxiety/depression. Each dimension is rated on five levels, ranging from “no problems” to “extreme problems,” allowing respondents to select the level that best represents their condition. The responses provide a comprehensive five-dimensional health state profile. In addition to these five dimensions, the EQ-5D-5L includes a visual analogue scale (VAS), which allows respondents to rate their current health status on a scale from 0 to 100 based on their subjective perception of their health.

Smoking behavior will be assessed using a self-designed questionnaire consisting of four multiple-choice questions, aimed at categorizing respondents based on their smoking habits (26). These questions are intended to determine whether the individual currently smokes, how many years they have been smoke-free, their daily smoking consumption, and their age when they started smoking. The first question asks: “Do you currently have a smoking habit?” The response options are: (1) Yes, I smoke regular cigarettes; (2) Yes, I smoke e-cigarettes; (3) I smoke both; (4) I used to smoke (currently quit); (5) I have never smoked. Based on the responses, participants will be classified into two groups: smokers (current smokers) and non-smokers (never smoked or quit).

Drinking behavior will also be evaluated using a self-designed questionnaire, which includes seven multiple-choice questions designed to gain detailed insights into the respondents’ drinking habits. These questions cover aspects such as whether the respondent drinks alcohol, their age at first use, age at cessation, types of alcohol consumed, daily alcohol intake, their average daily consumption before quitting, and any anxiety experienced during the quitting process. The respondents will be asked: “Do you currently drink alcohol, or have you drunk in the past?” The response options are: (1) Never drank; (2) Always drink; (3) Drank in the past but do not drink now; (4) Did not drink before, but now drink.

The Pittsburgh Sleep Quality Index Short Form (PSQI-SF) is a condensed version of the Pittsburgh Sleep Quality Index, specifically designed to assess an individual’s sleep quality (27). This scale consists of six items covering five key dimensions: sleep efficiency (items 1 and 2), sleep onset latency (item 3), sleep duration (item 4), sleep disturbances (item 5), and overall sleep quality (item 6). The sleep onset and wake-up time data are used to calculate sleep efficiency. The total score ranges from 0 to 15, with higher scores indicating poorer sleep quality, reflecting greater sleep difficulties.

The Family Communication Scale Short Form (FCS-SF) aims to assess the effectiveness of communication within the family (28). The scale consists of four items, measuring a single dimension, and uses a 5-point Likert scale ranging from 1 (strongly disagree) to 5 (strongly agree). The total score ranges from 4 to 20, with higher scores indicating better communication ability among family members, reflecting a healthier and more effective communication pattern.

The Chinese eHealth Literacy Scale (eHEALS) is a comprehensive measure to evaluate patients’ integrated knowledge, functional convenience, and perceived ability in searching, assessing, and utilizing eHealth information to solve everyday health-related issues (29). It has 5 items, 1 dimension, with a 5-point Likert scoring system from 1 (strongly disagree) to 5 (strongly agree). The range of total scores is from 5 to 25, with high scores reflecting a better individual eHealth literacy.

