## Discussion

5

This study is designed to systematically evaluate the effectiveness of the AI-HEALS intervention, delivered via the WeChat platform, in improving physiological indicators, mental health, and self-management behaviors among patients with COPD through a randomized controlled trial. Although previous interventions have provided some benefits for patients with COPD, long-term self-management remains challenging due to the complexity of the disease, psychological burden, and limited access to continuous, individualized support (9, 10). Existing mobile health interventions have attempted to address these issues. However, their effectiveness has often been constrained by high dropout rates, complex intervention procedures, or a narrow focus on selected behavioral outcomes (12, 13).

Against this backdrop, the present study integrates a 3-months AI-HEALS intervention grounded in the HAPA-MTM framework with a 9-months follow-up period to evaluate both the effectiveness and sustainability of behavior change. The use of artificial intelligence enables the delivery of tailored, timely, and scalable health education, while the integration with WeChat, a widely adopted communication platform, may enhance accessibility and user engagement. By addressing gaps in the literature regarding the long-term sustainability and practicality of digital self-management interventions for COPD, this study aims to contribute empirical evidence supporting the role of AI-enabled tools in chronic disease management.

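### Smoking is scored only as smoker versus non-smoker although daily amount and product are asked, so cutting down or changing product without quitting does not register; add daily amount beside cessation (minor)

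*Protocol article*

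**What the plan says.** Smoking enters the protocol article in four places.

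- **Section 2.8.2** lists it among the secondary outcomes: "Changes in self-management behaviors: including diet, physical activity, medication adherence, smoking management, alcohol management".
- **Section 2.10** describes the instrument as a "self-designed questionnaire consisting of four multiple-choice questions, aimed at categorizing respondents based on their smoking habits". The first question has five options: regular cigarettes, e-cigarettes, both, former smoker, never smoker. The remaining questions cover "how many years they have been smoke-free, their daily smoking consumption, and their age when they started smoking". The scoring rule follows: "Based on the responses, participants will be classified into two groups: smokers (current smokers) and non-smokers (never smoked or quit". All three current-use options therefore count as smoker. No use of daily consumption or product as an outcome is named.
- **Table 1 (section 2.9)** schedules the smoking form at baseline, end of intervention, and 3, 6 and 9 months after that.
- **Section 2.11** assigns the chi-square test to categorical data and two-sided 0.05 to all tests. For secondary outcomes it leaves a choice between mixed models and simpler comparisons.

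Section 2.4 sets the purpose of this phase: "the primary objective is not hypothesis testing but to estimate outcome variance and effect size with sufficient precision". It plans about 25 patients per group after attrition and 30 recruited per group.

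**The concern.** The third study objective is self-management behaviour, and the Discussion says the design is meant "to evaluate both the effectiveness and sustainability of behavior change". Reduced consumption is one form that such change could take. A patient who goes from 20 to 5 cigarettes a day, or from both products to one, is a smoker at both visits under the stated rule and shows no change. The form has already collected the information that would show it.

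The grouping also pools patients who never smoked, and so cannot quit, with patients who quit. A comparison across the whole arm is thereby diluted.

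At stake is whether the pilot's named smoking endpoint can show the kinds of change the programme might produce, and whether it yields a useful effect estimate for planning the main trial.

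**Working it through.** **1. The plan's own figure.** No power, smoking prevalence, quit rate or intake is stated. The only figure to reproduce is the recruitment target. Inflating 50 evaluable patients: 50/(1 − 0.10) = 55.6, so 56; 50/(1 − 0.20) = 62.5, so 63. The stated 60 lies inside 56 to 63 and implies attrition of 1 − 50/60 = 16.7%. It is in order.

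**2. What follows by logic alone.** Status takes two values, so any change within the current-use options, or in amount above zero, maps to smoker at both visits. This needs no assumption.

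**3. Size, under assumptions.** None of these inputs is in the article:

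- 40% of patients smoke at baseline: 0.40 × 25 = 10 per arm (evaluable) or 0.40 × 30 = 12 per arm (all recruited).
- Intake at baseline and follow-up is bivariate normal with mean 15 cigarettes a day, SD 8 and correlation 0.6, with values below 1 set to 1.
- The control quit rate is 10%, and quitters are set to 0.
- A cut multiplies follow-up intake in the intervention arm by (1 − cut).

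Status is tested by uncorrected chi-square on quit/not quit among baseline smokers. Amount is tested by ANCOVA: follow-up amount = a + b·arm + c·baseline amount. Both are two-sided at 0.05. Shares of simulated trials that reject:

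| Assumed effect | Smokers per arm | Status | Daily amount |
|---|---|---|---|
| 40% cut, quitting 10% in both arms | 10 | 1% | 44% |
| same | 12 | 1–2% | about 50% (49–54%) |
| 20% cut, quitting 10% in both arms | 12 | 1–2% | 15% |
| 40% cut, quitting 20% vs 10% | 12 | 6–8% | 59–60% |
| quitting only, 20% vs 10% | 12 | 7% | 7–8% |
| quitting only, 25% vs 10% | 12 | 12% | 10% |
| quitting only, 40% vs 10% | 10 | 28–30% | 20% |
| same | 12 | 39% | 24–25% |

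Ranges reflect repeated runs and how intakes near zero are generated. In the equal-quitting rows status has nothing to detect, so its 1% to 2% is simply the false-positive rate of chi-square with very few events.

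**4. Banding.** The questions are multiple choice, so daily amount may come in bands. The bands are not given. With illustrative bands (0, 1–10, 11–20, above 20, or one more band at the top) scored in order, the first two rows fall from 44% to about 33% and from about 50% to about 37–39%.

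**5. A second model as a check.** This one takes 25 patients per arm, with 30%, 50% or 70% smoking at baseline, gamma-distributed intake with mean 15, and status compared across the whole arm.

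- A 30% cut with equal quitting: status 5–7%; amount 25%, 39%, 52%.
- Quitting only, 40% vs 10%: status across the whole arm 12%, 22%, 36%; amount 16%, 28%, 36%; status restricted to baseline smokers 25%, 43%, 56%.

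The pattern is the same. The last item shows the gain from reporting cessation among baseline smokers.

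**The case against.** The strongest reply has four parts.

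- **The rule may not be the whole analysis.** Section 2.10 says how respondents are grouped. It does not say the other items are discarded, and section 2.11 leaves secondary analyses open. This stands in part. A reader might infer that a reduction will be scored as no effect, or that the pilot will yield no variance for consumption. The article supports neither: raw amounts are collected and can still be summarised. What remains is that status is the only smoking endpoint named.
- **Status is a legitimate endpoint.** Cessation is easy to interpret, and for a quitting effect it matches or beats daily amount. This stands in full. A reader might conclude that most of the available power is lost. That is true only where the effect runs wholly or partly through reduction, and replacing status with amount would lose power for cessation.
- **Quits can already be timed.** Because time smoke-free is asked in years, a reader might infer that quits during the trial cannot be dated. Table 1 repeats the form at baseline, end of intervention and three later visits, which places a quit to within about three months. The timing criticism falls.
- **The stakes are low.** This is one of many secondary outcomes, in a phase that disclaims hypothesis testing. This stands and sets the severity. It does not remove the point, since the pilot's stated purpose is to estimate effects and variances.

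**Conclusion.** The concern holds in a limited form. The one smoking endpoint named cannot register cutting down or a change of product, although the form asks about both.

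If the programme works through reduction, the loss is large under the assumed inputs: about 1–2% detection by status against about 44–54% by daily amount for a 40% cut with equal quitting (about 33–39% if banded). For a 20% cut the amount measure itself reaches only about 15%. If the programme works through quitting, nothing is lost.

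These figures rest on assumed smoking prevalence, intake, correlation and quit rates. The article gives none, so no power loss can be derived from it. Severity: minor.

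**What to change.** In sections 2.8.2 and 2.10:

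1. Keep cessation status, and report it among patients who smoke at baseline.
2. Add daily consumption at end of intervention among baseline smokers as a second smoking measure, alongside status and not in its place. Count quitters as 0 and adjust for baseline consumption. Analyse it on the item's own scale, as ordered bands if it is banded.
3. Tabulate moves between the five response options by arm, so that changes of product are visible.

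Asking smoke-free time in months rather than years is optional.

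The cost is a few lines of text and one more secondary comparison. No extra patients, visits or questions are needed. The downside is that self-reported amount is noisier than status, and patients know their allocation, so the added measure should be read as descriptive support for planning the main trial.
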